### Outcome measures

The primary outcome measures focused on evaluating the quality of chest compressions performed during cardiopulmonary resuscitation (CPR). These included:

Compression Rate: Measured in compressions per minute (cpm), with an optimal range defined as 100–120 cpm according to American Heart Association (AHA) guidelines.

Compression Depth: Recorded in millimeters, assessing whether compressions met the recommended depth of 51–61 mm.

Chest Recoil: Evaluated based on the proportion of compressions allowing complete chest recoil, important for effective blood flow during CPR.

Overall CPR Quality Score: The overall CPR quality score was automatically generated by the Q-CPR skill reporter system integrated with the Resusci Anne manikin. The software calculates a composite score (ranging from 0 to 0–100%) based on real-time assessment of four key parameters: compression rate, compression depth, recoil, and hand position accuracy. Each parameter contributes proportionally to the total quality score according to the system’s internal algorithm, which follows the American Heart Association (AHA) 2020 guidelines for high-quality CPR. Thresholds for performance classification were defined by the Q-CPR software as follows:• Good performance: Overall quality score ≥ 95%• Average performance: Overall quality score between 85%–94%• Poor performance: Overall quality score < 84%

These thresholds are automatically applied by the Q-CPR software to categorize the rescuer’s performance after each simulation session. The score thus represents an integrated measure of compression quality that reflects adherence to recommended CPR parameters.

Secondary outcome measures included:•The impact of metronome guidance on maintaining optimal compression rhythm.•The difference in CPR performance between pretest and post-test phases within and between groups.

These outcome measures were chosen to comprehensively assess the effectiveness of metronome guidance in enhancing CPR quality among novice nurses.

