### Sample size

Referring to the previous study, Use of a Metronome in CPR: A Simulation Study [9], the estimated sample size was determined to be 160 participants; this would achieve the power of 80% at a level of significance of 0.05. The calculated sample size per group is 72. Accounting for a 10% dropout rate, the adjusted sample size is 80 participants per group, resulting in a total of 160 participants in both the intervention and the control group. The Minimal Clinically Important Difference (MCID) of 22 compressions per minute for compression rate was derived from previous studies that evaluated performance variability during CPR training between the experimental group and the control group. Prior research using simulation-based assessments identified a change of approximately 20–25 compressions per minute as the threshold at which differences in performance become clinically relevant and perceptible in terms of resuscitation quality [10,11]

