### Data analysis

The data analysis was conducted using SPSS version 22, employing both descriptive and inferential statistics to address the study objectives and test the hypotheses. Descriptive statistics, including frequency, percentage, mean, and standard deviation, will be used to summarize demographic variables and baseline characteristics. Inferential statistical analyses will be applied to evaluate the impact of metronome-guided CPR on novice nurses. Categorical comparisons will not be done, as the samples are almost similar age groups. Repeated measures ANOVA will be utilized to assess within-group and between-group differences over time in key CPR quality indicators such as compression rate, depth, recoil, and overall performance. A chi-square test will be performed for the post-test. Paired t-tests will be conducted to compare pretest and post-test scores within each group, while independent t-tests will assess differences between the intervention and control groups in the post-test phase. The level of statistical significance was set at *p* < 0.05. Results will be presented using tables and graphs to facilitate clarity and interpretation.

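### Four unranked primary outcomes are tested by overlapping methods at one unadjusted 0.05, and neither an outcome nor a test is named as deciding the hypothesis

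*Protocol article*

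**What the plan says.** The Outcome measures section opens in the plural: "The primary outcome measures focused on evaluating the quality of chest compressions performed during cardiopulmonary resuscitation (CPR". Four items follow, with no order of importance:

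- rate ("Compression Rate: Measured in compressions per minute (cpm), with an optimal range defined as 100–120 cpm");
- depth ("Compression Depth: Recorded in millimeters, assessing whether compressions met the recommended depth of 51–61 mm");
- the proportion of compressions with complete recoil;
- an overall score from the manikin software, built from rate, depth, recoil and hand position.

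The same section places differences between pre-test and post-test, within and between groups, among the secondary outcomes.

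The Data analysis section assigns repeated measures ANOVA to all four indicators by name. It adds paired t-tests within each arm and independent t-tests between arms at post-test. It also says "A chi-square test will be performed for the post-test" without naming the variable. The only threshold is this: "The level of statistical significance was set at *p* < 0.05".

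The Sample size section gives one effect, 22 compressions per minute, which "for compression rate was derived from previous studies". It does not call rate the sole primary outcome. The abstract states one broad hypothesis, that metronome users will show significantly higher compression quality.

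**The concern.** A single hypothesis about compression quality is to be judged from four primary outcomes, each open to more than one between-arm test at 0.05. The article does not say which result settles it, nor whether one success is enough or all four are needed. If one is enough, the 5% level describes each test but not the trial's conclusion.

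The overall score adds a further difficulty. Because it is computed partly from rate, depth and recoil, a positive score alongside a positive component is not a second, independent confirmation.

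**Working it through.** **The plan's own figure.** 72 / (1 − 0.10) = 80 per arm, or 160 in total. This reproduces. The 72 cannot be checked, because no SD is given.

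**Inputs from the article.** Four primary outcomes; threshold 0.05, taken as two-sided because no side is stated; 80 per arm.

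**Assumptions that the article does not supply.** Any one significant result counts as success. The correlation between outcomes is 0 to 0.8, and the correlation between pre-test and post-test is 0.3 to 0.7.

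**Closed form, four independent tests.**
- Either direction: 1 − 0.95^4 = 0.185.
- Favouring the metronome only: 1 − 0.975^4 = 0.096, against 0.025 for one test.

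**Simulation with no true effect on any outcome** (80 per arm, 4,000 trials per setting). Each cell gives the percentage of trials with at least one p < 0.05, as a range over the pre/post correlations. Simulation error is about 0.5 to 0.8 points.

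| Correlation between outcomes | Four post-test t-tests | + group-by-time interaction | + ANOVA group effect | t-tests, favouring metronome | t-tests + interaction, favouring metronome |
|---|---|---|---|---|---|
| 0 | 18.0–19.0 | 30.7–33.6 | 38.0–38.6 | 9.6–9.9 | 16.5–17.9 |
| 0.3 | 17.3–18.0 | 29.8–30.0 | 34.6–37.2 | 8.6–9.2 | 14.9–15.6 |
| 0.5 | 14.5–15.9 | 25.6–27.2 | 30.8–32.8 | 6.8–7.7 | 11.9–13.8 |
| 0.8 | 10.2–11.2 | 19.2–20.3 | 22.2–24.9 | 4.8–5.8 | 9.4–10.0 |

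A single post-test t-test in the same runs gave 4.3–5.4%, as it should. The last two columns treat higher as better. For rate and depth the target is a range, so they are only a guide to what would be reported as an improvement.

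The shared components of the overall score make high correlations plausible. That moves the error rate towards the lower rows, not the upper ones.

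**What a correction would cost.** Bonferroni over four uses 0.05 / 4 = 0.0125 per test and gives 1 − 0.9875^4 = 0.049 if the tests are independent. The power loss depends on the missing SD:

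- Solving back from 72 per arm at 80% power: SD = 22 / [(1.960 + 0.842) × √(2/72)] ≈ 47 cpm. The expected z is then 2.802 against a critical 2.498, so power is about 62%.
- With an SD of 20 cpm, which is also only an assumption, the expected z is 22 / (20 × √(2/72)) = 6.6. Almost no power is lost.

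The article does not allow a choice between these.

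**The case against.** **Pre/post differences are listed as secondary.** This covers the paired t-tests and, on a natural reading, the repeated measures ANOVA, which would leave the post-test comparison as primary. It is a fair point, and it weakens the case for the ANOVA columns. But the article only suggests this and does not say it, and the Data analysis section applies the ANOVA to the primary outcomes by name. Even on this reading, four unadjusted t-tests remain.

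**No rule says that one success is enough.** This is correct. The abstract expects gains in accuracy, depth and consistency together. If all four outcomes had to be significant, there would be no inflation. The article does not state that rule either, so the percentages are conditional.

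**A hierarchy may sit in an analysis plan that is not shown.** It may, but it would have to be reconciled with an article that declares four primary outcomes and one threshold.

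**Stronger readings that the documents do not support.**
- A reader might take the two-sided figures, up to nearly 40%, as the chance of falsely claiming that the metronome improves compressions. They count significance in either direction. For favourable results the rate is about half as large.
- A reader might count a fixed dozen or more p-values. Only the ANOVA sentence names the four indicators. The variables for the t-tests and the chi-square are inferred.
- A reader might treat the fall in power to about 62% as a planned quantity. It rests on an SD that the article never gives.
- A reader might say that the overall score can turn positive through rate alone. That depends on the software's internal algorithm, which is not described. If rate truly improved, the question would be what the score means, not false-positive error.

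**Conclusion.** The point stands as a defect in what the article fixes: several unranked primary outcomes, overlapping tests, one unadjusted 0.05 and no deciding rule.

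If any one significant result may count, the two-sided chance of at least one false positive is about 10–19% for four post-test t-tests. It is about 20–39% if the ANOVA interaction and group effect may also count. For results favouring the metronome it is roughly 5–10%, or 9–18% with the interaction, against 2.5% for a single test. That is about a two- to four-fold inflation on the t-tests alone (5 / 2.5 to 10 / 2.5).

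These ranges rest on assumed correlations and an assumed success rule. They show the order of the problem and are not properties that the article itself determines.

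**What to change.** 1. Name one primary outcome and one between-arm test of it. Compression rate is the outcome that the Sample size section addresses. If rate is instead scored against the 100–120 cpm range, that is a different endpoint from a 22 cpm difference, and the sample size justification must be restated for it.
2. Test the remaining outcomes in a fixed order or with Holm, using one named between-arm test for each.
3. Label the paired t-tests and the chi-square as descriptive.
4. State whether the choice was made before the data were seen. The Study design section gives the study period as November 2023 to March 2024, and the randomisation section reports the enrolment of 160 as past. If the choice came after sight of the data, keep all four outcomes as primary under Holm (thresholds 0.05/4, 0.05/3, 0.05/2 and 0.05 in order of p-value) rather than picking one now.

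**Cost.** The text change is short and needs no extra participants. Either the other outcomes lose standalone primary status, or some power is lost under Holm. The size of that loss cannot be computed from the article, because no SD is given.

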### Data analysis

The data analysis was conducted using SPSS version 22, employing both descriptive and inferential statistics to address the study objectives and test the hypotheses. Descriptive statistics, including frequency, percentage, mean, and standard deviation, will be used to summarize demographic variables and baseline characteristics. Inferential statistical analyses will be applied to evaluate the impact of metronome-guided CPR on novice nurses. Categorical comparisons will not be done, as the samples are almost similar age groups. Repeated measures ANOVA will be utilized to assess within-group and between-group differences over time in key CPR quality indicators such as compression rate, depth, recoil, and overall performance. A chi-square test will be performed for the post-test. Paired t-tests will be conducted to compare pretest and post-test scores within each group, while independent t-tests will assess differences between the intervention and control groups in the post-test phase. The level of statistical significance was set at *p* < 0.05. Results will be presented using tables and graphs to facilitate clarity and interpretation.

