### Randomisation, allocation concealment, and blinding

A total of 180 participants were assessed for eligibility, and 20 were excluded (12 did not meet the inclusion criteria, and 8 declined to participate). The remaining 160 participants were enrolled in the study. The flow of participants through the study is presented in Fig. 1 (CONSORT flow diagram). A block randomization was utilized to ensure balanced allocation of participants between the intervention and control groups. The total sample was separated into 16 blocks, with each block containing 10 participants—5 assigned to the study group (metronome-assisted CPR) and 5 to the control group (standard CPR without metronome guidance). This approach was chosen to maintain equal group sizes throughout the enrollment process and to minimize potential biases.

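### Data analysis rules out categorical comparisons without limit, then requires a post-test chi-square test on an unnamed variable; whatever that variable is, the test ignores the pre-test

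*Protocol article*

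**What the plan says.** In the Data analysis section, one sentence assigns descriptive statistics to demographic and baseline variables. The next announces inferential analyses of the metronome's effect. Directly after that comes "Categorical comparisons will not be done, as the samples are almost similar age groups". One sentence on repeated measures ANOVA follows, and then "A chi-square test will be performed for the post-test". No variable, table layout or type of chi-square test is given. The section also plans paired t-tests within groups and independent t-tests between groups at post-test, and closes with "The level of statistical significance was set at *p* < 0.05".

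The Outcome measures section lists the overall CPR quality score among the primary outcome measures and attaches classes to it: "Thresholds for performance classification were defined by the Q-CPR software as follows". Good is 95% or more, Average is 85% to 94%, and Poor is below 84%. The same section gives target ranges for rate (100–120 cpm) and depth (51–61 mm). It does not connect the classes or the ranges to the chi-square test.

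**The concern.** A chi-square test is a categorical comparison, so the two sentences cannot both be followed to the letter. Similar ages give no reason to omit an outcome comparison. For baseline variables, the sound reason not to test is that the groups are randomised.

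An analyst could therefore justify either running or omitting the test, and if running it would have to choose the variable. The Study design section dates the study November 2023 to March 2024, while the analysis is largely written in the future tense. An open choice of this kind could thus be made with the data in hand. Nothing in the article shows that it was.

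The second question is whether chi-square is a good test here. It uses none of the pre-test information collected from every participant and gives no direction or size of effect. On ordered classes it also discards the order, although the Expected outcome paragraph states a directional hypothesis.

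**Working it through.** **The plan's own figure.** The Sample size section says "The calculated sample size per group is 72" and "Accounting for a 10% dropout rate, the adjusted sample size is 80 participants per group". Check: 72 / (1 − 0.10) = 80 per group, and 2 × 80 = 160. This reproduces. The stated difference of 22 compressions per minute concerns compression rate, so the sample size does not rest on a class table.

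**Possible targets of the chi-square test**

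- Good/Average/Poor by arm: a 2x3 table with ordered columns and 2 df. It is the only explicit participant-level classification in Outcome measures.
- Rate within 100–120 cpm, or depth within 51–61 mm, yes/no by arm: a 2x2 table with 1 df and no order to lose.

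**Cost of ignoring order, if the target is the 2x3 table.** From the article: 80 per arm and alpha 0.05. Assumed, because the article gives neither: a two-sided test, the control class shares, and a common odds ratio (OR) for a better class.

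Example: control shares Poor/Average/Good 50/30/20%, OR 2.

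- Intervention shares: the cumulative odds of Poor are 0.5/0.5 = 1, halved to 0.5, so Poor is 1/3. The cumulative odds of Poor or Average are 0.8/0.2 = 4, halved to 2, giving 2/3. The intervention arm is therefore one third in each class.
- Pearson noncentrality = n × Σ(p−q)²/(p+q) = 80 × (0.0333 + 0.0018 + 0.0333) = 5.47. On 2 df the power is 54%.
- Trend test with scores 0, 1, 2: means 0.7 and 1.0, pooled variance 0.661. Noncentrality = 80 × 0.3² / (2 × 0.661) = 5.45. On 1 df the power is 65%.

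The two noncentralities are almost equal; the loss comes from spending a second degree of freedom. In general, 80% power needs noncentrality 7.85 on 1 df and 9.63 on 2 df. The ratio is 1.23, or up to about 23% more participants. At 7.85 the 2-df test has 71% power.

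Simulation with 20,000 trials per scenario and 80 per arm (losses from unrounded figures):

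| Control Poor/Average/Good | OR | Chi-square | Trend | Loss (points) |
|---|---|---|---|---|
| 50/30/20 | 1.5 | 21% | 28% | 6.2 |
| 50/30/20 | 2 | 54% | 65% | 10.4 |
| 50/30/20 | 2.5 | 80% | 87% | 7.3 |
| 50/30/20 | 3 | 93% | 96% | 3.4 |
| 80/15/5 | 1.5 | 14% | 18% | 3.9 |
| 80/15/5 | 2 | 38% | 46% | 7.9 |
| 80/15/5 | 3 | 82% | 88% | 5.3 |
| equal thirds | 2 | 54% | 65% | 10.5 |

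With no effect, both tests rejected in about 5% of trials.

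**Where the comparison reverses.** If Poor is unchanged and participants move from Average to Good (50/30/20 against 50/10/40), chi-square has 93% power and trend 30%. For 30/40/30 against 42/16/42 the figures are 88% and 5%.

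**Class limits.** Scores from 84% to below 85%, and above 94% to below 95%, belong to no printed class. If scores are whole percentages, only 84% is left out.

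**The case against.** The strongest reply is that the two sentences do not really collide. The age rationale makes sense only for demographic comparisons, the sentence stands close to the one on demographic summaries, and the chi-square sentence is an explicit instruction about the post-test. This is probably what was meant. It does not remove the defect: the sentence carries no such limit, it directly follows the announcement of inferential analyses, and even on this reading similar age is the wrong reason.

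A reader might go further and infer that the plan applies an unordered test to Good/Average/Poor and so loses power. The article does not support that as a finding. It never links the chi-square to those classes. For a 2x2 target the loss is nil, and for some shifts in a 2x3 table chi-square is the better test, as the working shows. The class shares and odds ratios are assumptions throughout.

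It is also fair that the overall score is analysed ungrouped by repeated measures ANOVA, which includes the pre-test, and that independent t-tests compare the arms at post-test. Direction and baseline are therefore largely covered elsewhere. The Intervention and data collection section also reports efforts to blind the data analysts. This limits the consequence, but it does not settle whether the categorical test is to be done or on what.

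**Conclusion.** The point holds as a literal self-contradiction together with an unnamed test variable. Two things stand without any assumption: as worded, the plan both excludes and requires a categorical comparison; and the chi-square test ignores the pre-test whichever variable is meant.

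The loss of power is conditional. It requires a Pearson 2x3 test of the ordered classes and a proportional-odds shift. Over the scenarios run, with 80 per arm and two-sided 0.05, it is 3.4 to 10.5 percentage points. It should not be presented as an error in the plan.

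The practical weight is modest. The sample size rests on compression rate, and the overall score is tested ungrouped elsewhere. It remains a cheap and worthwhile correction.

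**What to change.** 1. Limit the first sentence, for example: *Demographic and baseline characteristics will be described by arm and not tested, because the groups are randomised.*
2. Name the post-test categorical variable.
3. Replace the chi-square sentence with a supportive logistic model for that variable, adjusted for the corresponding pre-test value and reported as an odds ratio with 95% CI. Use proportional odds if the variable is Poor < Average < Good, adjusted for the pre-test overall score. Use binary logistic regression if it is yes/no. A linear trend test is an acceptable unadjusted version for the three classes.
4. Before the classes are used, state limits that leave no score unassigned, taken from the software's own rule.

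The cost is two sentences of analysis wording and a correction to the printed limits, with no new data. The downside is reliance on the proportional-odds assumption and less sensitivity to non-monotone differences. Showing the class counts by arm beside the model would let a reader see such a pattern.

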### Intervention and data collection

Following randomization, all participants did a 2-minute pretest of compression-only cardiopulmonary resuscitation on a Q-CPR manikin without any metronome guidance. This pretest was conducted to establish a baseline measurement of chest compression quality for both groups under identical conditions. Data for each participant was recorded using the Q-CPR manikin, connected to the Resusci Anne Wireless Skill Reporter software and a personal computer skill reporting system (Laerdal Medical AS, Stavanger, Norway). After a 20-minute rest interval, to prevent fatigue from affecting post-test performance, the intervention group performed a 2-minute compression-only CPR session on the QCPR manikin, this time guided by a metronome set to 110 beats per minute (BPM), delivered through a mobile phone application. In contrast, the control group completed the post-test without any metronome assistance, replicating standard CPR practice.

The system measured key CPR quality indicators, focusing on three core components: adequate chest compression depth, compression rate, and full chest recoil. In addition to these specific metrics, the software generated an overall performance score based on each participant’s adherence to CPR guidelines. This ensured an accurate and objective assessment of CPR quality, providing consistent data for evaluating the impact of metronome guidance on chest compression performance.

To ensure objective evaluation, both groups underwent a post-test assessment measuring key CPR performance indicators, including compression rate, depth, and recoil. While full blinding of participants was not feasible due to the audible metronome in the study group, efforts were made to blind the data analysts to group assignments during the evaluation phase to minimize assessment bias.

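### The planned arm comparisons are valid but less precise than they could be: none adjusts the post-test for the pretest, and the ANOVA term that tests efficacy is not named

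*Protocol article*

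**What the plan says.** The Data analysis section of the protocol article sets out these comparisons of means for the compression outcomes:

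- ANOVA: "Repeated measures ANOVA will be utilized to assess within-group and between-group differences over time". It does not say whether the group main effect or the group-by-time interaction is the test of efficacy.
- Within arms: "Paired t-tests will be conducted to compare pretest and post-test scores within each group".
- Between arms: "independent t-tests will assess differences between the intervention and control groups in the post-test phase".

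A chi-square test at post-test is also planned. No analysis adjusts the post-test for the pretest, and none is named as the one that decides the arm comparison.

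The pretest exists for everyone. Under Intervention and data collection the article says: "This pretest was conducted to establish a baseline measurement of chest compression quality for both groups under identical conditions". The same section places the pretest after randomisation, and Study design describes the trial as open-label. Under Outcome measures, pretest-to-post-test differences, both within and between groups, are a secondary outcome.

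**The concern.** Each participant's own earlier performance on the same manikin is likely to predict the later one. A comparison that leaves it out carries avoidable noise. In the unadjusted t-test, a chance difference between arms at pretest also stays in the point estimate.

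The ANOVA does use the pretest, but its two between-arm terms answer different questions. The group main effect averages post-test with pretest, where the metronome can have had no effect, and so estimates half the difference. The group-by-time term estimates the whole difference, but as a change score, which is noisier than covariance adjustment.

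The paired t-tests measure the change from a first to a second attempt after a 20-minute rest. In the metronome arm that change contains practice as well as the metronome. A significant result in one arm and not the other is not evidence that the arms differ.

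At stake are the width of the confidence interval and the clarity of the conclusion, not the type I error of the between-arm tests.

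**Working it through.** **Inputs from the Sample size section.** 80% power at 0.05 ("this would achieve the power of 80% at a level of significance of 0.05"); 72 per arm ("The calculated sample size per group is 72"); 80 per arm after dropout ("Accounting for a 10% dropout rate, the adjusted sample size is 80 participants per group"); and 22 compressions per minute ("The Minimal Clinically Important Difference (MCID) of 22 compressions per minute for compression rate"), which is not said to be the effect behind the 72.

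**Not stated, so assumed.** A two-sided test, equal variances, and a pretest/post-test correlation r of 0.3, 0.5 or 0.7. No SD or standardised effect d is given.

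**The plan's own figures.** The dropout step reproduces: 72 / (1 − 0.10) = 80, and 2 × 80 = 160. The 72 cannot be checked without an SD. It can be inverted: d = (1.960 + 0.842) × √(2/72) = 0.467. If the difference is 22 per minute, SD = 22 / 0.467 = 47.1 per minute (53.1 if the test were one-sided).

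**Effective standardised effect of each between-arm test:**

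- post-test t-test: d
- ANOVA group main effect: 0.5d / √((1 + r)/2)
- ANOVA group-by-time (identical to a change-score test): d / √(2(1 − r))
- ANCOVA of post-test on arm and pretest: d / √(1 − r²)

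Power = Φ(effective effect × √(72/2) − 1.960), where √(72/2) = 6. For ANCOVA at r = 0.5: 0.467 / √0.75 = 0.539; 0.539 × 6 = 3.235; Φ(1.275) = 89.9%.

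| Power at 72 per arm | r = 0.3 | r = 0.5 | r = 0.7 |
|---|---|---|---|
| Post-test t-test | 80.0% | 80.0% | 80.0% |
| Group-by-time | 65.8% | 80.0% | 95.1% |
| ANCOVA | 83.6% | 89.9% | 97.5% |
| Group main effect, if it were used | 41.2% | 36.6% | 33.0% |

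For 80% power, ANCOVA would need 66, 54 or 37 per arm instead of 72. Group-by-time is weaker than the plain post-test t-test whenever r is below 0.5.

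**Simulation (10,000 runs, 72 per arm).** All four between-arm tests hold about 5% type I error, and the powers agree with the table to within about one percentage point.

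**Sensitivity to the SD.** If the difference is 22 per minute and the SD is 25 or 30 (assumed), the post-test t-test already has 99.95% or 99.3% power, so ANCOVA can add less than one percentage point.

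**Sensitivity to equal variances.** A fixed beat may shrink the spread of rate in the metronome arm. In one simulated case (metronome-arm SD 0.3 of control, r = 0 there and 0.6 in control, difference 0.3 control SDs), power was 67.7% for the post-test t-test and 75.6% for ANCOVA.

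**Paired t-tests.** With no difference between arms, the two paired tests disagree (one significant, the other not) in 9.7, 9.3 and 9.0% of simulated trials for r = 0.3, 0.5 and 0.7 when there is no practice effect. With a shared practice gain of 0.25 SD (assumed) they disagree in 48.4, 48.8 and 35.1%.

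**The case against.** The strongest reply is that the plan already contains a sound arm comparison that uses the pretest. Differences between groups over time most naturally means the group-by-time term, and the secondary outcome on pretest-to-post-test differences points the same way. That stands. A reader might infer that the planned comparison either throws the pretest away or halves the effect. The article does not support this, because it nowhere makes the group main effect the efficacy test. The 33 to 41% powers therefore describe one possible use of an unnamed term, not the trial's planned power. Leaving the term unnamed would, alone, be a detail for the full protocol or analysis plan. The point rests on the methods the article does list, none of which is covariance adjustment.

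The paired t-tests are correctly described as within-group, and the article draws no efficacy conclusion from them. That also stands: the risk lies in later interpretation.

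The size of the gain rests on an unstated SD and correlation. For rate it could be negligible. For depth, recoil and the overall score it cannot be calculated from the article.

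Nor is adjustment entirely free. The pretest follows randomisation in an open-label trial. The article does not say whether participants knew their arm when they did it. If they did, pretest effort could differ by arm and adjustment could carry that into the estimate. Group-by-time shares this weakness; the post-test t-test does not. This is a reason to keep the unadjusted comparison as a check, not to leave the pretest unused.

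**Conclusion.** The point holds as one of efficiency and clarity. The post-test t-test is valid but does not use the pretest. Group-by-time, if that is what is meant, is valid but less efficient than ANCOVA at each correlation tried. The group main effect, if used, would estimate half the effect. The paired t-tests do not compare arms.

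Under the assumptions above, ANCOVA raises power over the post-test t-test by about 4, 10 and 18 percentage points at r = 0.3, 0.5 and 0.7 (83.6, 89.9 and 97.5% against 80.0%). Over group-by-time the gain is about 18, 10 and 2 points. These figures depend on d = 0.47, which is inferred from 72 per arm. With 22 per minute as the difference, that d implies an SD of about 47 per minute; at 25 to 30 the gain for rate is negligible.

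A reader might go further and conclude that the planned between-arm results would be biased or have an inflated false-positive rate. Nothing in the document supports that.

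**What to change.** For each continuous outcome (compression rate, depth, recoil proportion, overall score):

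1. Make the between-arm analysis an ANCOVA of the post-test value on arm and pretest value, and report the adjusted difference with its 95% confidence interval.
2. Do not use the ANOVA group main effect as a test of efficacy. If the ANOVA is kept, name group-by-time as its between-arm term.
3. Report within-arm changes descriptively, without separate significance tests.
4. Keep the unadjusted post-test comparison as a sensitivity analysis, because the pretest was taken after randomisation without blinding of participants.

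The cost is small: no new data are needed, the model uses one extra degree of freedom, and SPSS fits it. The study period given under Study design ended in March 2024, so sessions appear complete. The change should be dated, disclosed as an amendment, and made while the analysts are still blinded to arm. If results have already been seen by arm, the adjusted analysis should be labelled post hoc.
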